## Discussion

3

EGb COCOS will be performed to determine the suitability of EGb 761® as a treatment for cognitive impairment associated with PCS in a randomised, placebo-controlled trial.

The cognitive impairment observed in PCS is thought to be driven by a complex and multifactorial pathophysiology, including persistent neuroinflammation, oxidative stress, mitochondrial dysfunction, and vascular and endothelial dysfunction (Chen et al., 2025; Mueller and Müller, 2024; Peluso and Deeks, 2024). EGb 761® is a multi-target agent whose broad pharmacological spectrum provides a consistent mechanistic rationale for its use by addressing these pathological pillars (Mueller and Müller, 2024; Owens et al., 2024). Specifically, EGb 761® exhibits potent anti-inflammatory properties that counter the microglial activation and cytokine release (e.g., IL-6) (Sun et al., 2024), which have been postulated to play a central role in post-COVID-19 neuroinflammation (Mueller and Müller, 2024; Peluso and Deeks, 2024). EGb 761® has also been shown to exhibit significant antioxidant activity, mitigating oxidative stress and mitochondrial dysfunction (Eckert et al., 2005). Furthermore, EGb 761® has beneficial effects on the vascular system, including the protection of endothelial cells and reduction of blood viscosity (Zhang et al., 2017; ErdinҪler et al., 1996). Taken together, these properties of EGb 761® could directly address the impairment of neurovascular coupling (Owens et al., 2024). Neurovascular coupling refers to the coordinated interplay between brain parenchymal cells and vascular cells that constitute the neurovascular unit. Under normal conditions, it adjusts the cerebromicrovascular blood flow to meet the neuronal demands on energy and nutrients. Neurovascular uncoupling has been proposed as a critical component of cognitive dysfunction in PCS (Owens et al., 2024). Finally, EGb 761® enhances neuroplasticity and promotes neuroprotection, in part by increasing the levels of brain-derived neurotrophic factor (BDNF) (Xu et al., 2007; Akanchise and Angelova, 2023), which is known to be diminished in PCS (Chen et al., 2025). Through these pleiotropic actions, EGb 761® may be a mechanistically plausible and low-risk therapeutic option for PCS-associated cognitive impairment (Owens et al., 2024; Zifko et al., 2022).

Whilst most placebo-controlled trials supporting the efficacy of EGb 761® in mild cognitive impairment and dementia used treatment durations of 22 to 52 weeks, clinical benefits on cognition have been reported with 6 to 12 weeks of treatment in healthy individuals and patients with very mild cognitive impairment (Kaschel, 2009; Grass-Kapanke et al., 2011; Kaschel, 2011; Beck et al., 2016). Cognitive impairment in PCS has been reported to improve spontaneously within 6 to 12 months in a majority of patients. Therefore we concluded that a clinical effect not emerging within 3 months of treatment would be of limited clinical benefit in this population and selected a 12 week treatment schedule.

Strengths of the present trial include its large sample size, randomisation, triple-blinding, and placebo-comparator arm. According to the WHO, PCS occurs in individuals with a history of probable or confirmed SARS-CoV-2 infection continuing at least 3 months from the onset of COVID-19, with symptoms lasting at least 2 months, that cannot be explained by an alternative diagnosis (World Health Organization, 2021). By using this definition in the inclusion criteria, this clinical trial aims to include patients with a documented history of probable or confirmed SARS-CoV-2 infection. The findings of the trial may prove highly valuable for patients with cognitive impairment associated with PCS. In addition, the methodology implemented in the study may be useful for future trials addressing cognitive issues in PCS.

The trial outcomes and assessments are easy to record, location-independent, and applicable across a diverse patient population. A narrative review of pharmacological studies evaluating treatment options for neuropsychiatric symptoms in PCS shows the current wide range of cognitive endpoints used (Lejay et al., 2023). No standardised approach has yet been established (see text Footnote 1). Notably, there is accumulating evidence of a discrepancy between subjective cognitive complaints and objective cognitive impairment in patients with PCS (Bland et al., 2024). Subjective complaints are more likely to be reported than objectively detected (Tarantini et al., 2025; Schild et al., 2023), highlighting the limitations of cognitive testing in this patient population. In the present trial, an exploratory trial design will be used that includes a range of validated cognitive endpoints (e.g., Digit span Forward and Backward, Verbal Fluency test, Symptom Burden Questionnaire for long COVID) (SBQ-LC, module “Memory, Thinking and Communication”). These have been chosen to cover both general cognitive impairment and COVID-19-associated cognitive impairment. Additionally, other symptoms linked to cognitive complaints and mediating the relationship between subjective cognitive symptoms and objective cognitive performance will be examined (Delgado-Alonso et al., 2025a; Denno et al., 2025). Post-exertional malaise (PEM) is a key feature of PCS and an important consideration for trial participants. One measure to limit the PEM risk was to restrict cognitive testing to the minimum required to achieve the trial objective. Therefore we restricted cognitive testing to those domains that have been reported to be affected most in PCS and to be most relevant for everyday life in PCS (Delgado-Alonso et al., 2022, Delgado-Alonso et al. 2025a, Panagea et al., 2025). Validated tests with available versions in Spanish, Polish, and German were selected for working memory (Digit Span Forward and Backward), verbal learning (California Verbal Learning Test), executive function (Trail-Making Test), verbal fluency, and sustained attention (d2 Test of Attention – Revised). Applying these tests as a fixed battery will allow to assess fatigability, a key feature of cognitive complaints in PCS that is poorly captured by other validated cognitive tests. Whilst this approach might miss treatment effects in cognitive domains not tested, such as visuospatial abilities or social cognition, the cognitive battery covers the domains most relevant in PCS.

Consultation on the trial design and planned tests and procedures was requested from the German patient organisation “Long COVID Deutschland” (LCD). Two measurements have been implemented in the trial design, based on their recommendation. Firstly, the electronic case report form now includes a section for the recording of any self-medication and the use of food or dietary supplements, vitamins, and minerals due to the widespread use of such products amongst patients with PCS. Secondly, the visits to the trial sites will be standardised to reduce avoidable burden on participants.

EGb 761® is generally well tolerated. In clinical trials, adverse events have not been reported more frequently than with placebo (Tan et al., 2015). Known contraindications and warnings (e.g., pregnancy, hypersensitivity to the investigational product, haemorrhagic diatheses, coagulation disorder, concomitant use of anticoagulants) are exclusion criteria for the trial.

Symptoms of depression and anxiety are frequent in PCS (Bidhendi-Yarandi et al., 2025; Seighali et al., 2024). In samples from the general population, both depression and anxiety are associated with impairments in cognitive function, e.g., (Lindert et al., 2021; Suddell et al., 2023). By contrast, in a large PCS cohort, mild to moderate depression had only a limited impact on objective cognitive performance (Delgado-Alonso et al., 2025a; Delgado-Alonso et al., 2022; Delgado-Alonso et al., 2025b). The interpretation was that in PCS fatigue and other factors have stronger effects on cognition than anxiety and depression. In PCS, fatigue and depression are highly correlated and can be difficult to distinguish (Stallmach et al., 2022). Considering that fatigue is a cardinal feature of PCS, and that depression and anxiety are very frequent in PCS, we decided to exclude only patients with severe depression or anxiety. Excluding patients with (treated) mild-to-moderate anxiety and depression would have excluded a large part of the PCS population. The vast majority of patients seeking medical care for PCS meets our liberal inclusion criteria of at least mild depression (PHQ-9 score> = 5) or anxiety (GAD-score> = 5) (Stallmach et al., 2022; Downer et al., 2024). Our main strategy to mitigate potential confounding by concomitant mild-to-moderate depression and anxiety as well as their treatments is trial design. Potential effects of known and unknown confounders on outcomes will occur in both treatment groups in a randomised parallel group trial. In case treatment groups will be unbalanced in important known potential confounders despite randomization, statistical analysis will account for such differences.

Patients that were on mechanical ventilation in an ICU during acute SARS-CoV-2 infection are excluded because we want to avoid confounding with post intensive care syndrome (PICS). Because PCS and PICS might differ in pathophysiology (Fleischmann-Struzek et al., 2024) and PCS also occurs after non-severe acute COVID-19, excluding ICU/mechanical ventilation results in a more post-COVID specific sample.

Cognitive performance typically declines in middle-aged and elderly people in the general population. In post-COVID syndrome (PCS) however, subjective and objective cognitive impairment has been reported over all adult age groups (Gonzalez Aleman et al., 2025). Whilst age is a risk factor for cognitive impairment in PCS, cognitive impairment might have a more profound effect on daily life in younger cohorts (Davis et al., 2021). Therefore treatment of cognitive impairment in PCS is clinically relevant over all age groups and we include adult patients without further age restriction. Because age-specific phenotypes have been reported for cognitive impairment in PCS (Gonzalez Aleman et al., 2025), we plan a subgroup-analysis by age.

The trial design has several limitations. First, to limit the burden to patients and the duration of trial visits, a decision was taken not to conduct imaging studies and not to collect biological samples. As a consequence, we will be able to assess clinical effectiveness, but we will be unable to explore potential modes of action. Second, for the reasons discussed above the statistical analysis will be exploratory in nature, and no formal hypothesis testing for confirmatory claims will be performed. With an observation time of 12 weeks we will not be able to evaluate long-term effects. Excluding patients with a history of prolonged PEM excludes ME/CFS-like phenotypes and therefore limits generalizability of results. In case we will observe efficacy and good tolerability in the present trial, these limitations need to be addressed in future studies.

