### Sample size calculation

2.8

Currently, there is very limited data on the use of EGb 761® in patients with cognitive impairment associated with PCS (Gebetsroither, 2024; Zifko et al., 2022). Therefore, the sample size was determined considering a small standardised mean difference (treatment effect size) according to Cohen’s d (Cohen, 1988).

A treatment effect size was reported as 0.52 for EGb 761® compared to placebo for cognition in a meta-analysis of dementia trials (Gauthier and Schlaefke, 2014). Because patients with dementia are more cognitively impaired and represent a more homogeneous population compared to patients with PCS, the treatment effect size is assumed to be smaller in PCS. To detect at least one significant outcome in the two cognitive domains memory and executive functioning assuming a treatment effect size of at least 0.25, a correlation of 0.3 to 0.4 between both domains (Napryeyenko et al., 2007; Ihl et al., 2011; Herrschaft et al., 2012; Nikolova et al., 2013), a statistical power of at least 80%, a local 2-sided significance level of 0.05, and a dropout rate of about 15%, 400 patients need to be randomised (R package rPowerSampleSize Version 1.0.2, R version 4.3–2 [2023-03-15]).

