### Statistical methods

2.11

The efficacy endpoints will be summarised using summary statistics in line with estimand strategies. Intercurrent events considered in this trial are treatment discontinuation, treatment noncompliance and initiation or adjustment of prohibited concomitant medication. The hypothetical strategy will be used to estimate the effects attributable to trial treatment without influence from prohibited medication and where the treatment is taken as intended. For the safety endpoints, the incidence of participants with AEs, adverse drug reactions, and serious AEs for the safety population will be summarised by treatment arms and exposure phases. The analysis will be exploratory in nature, and no formal hypothesis testing for confirmatory claims will be performed. Therefore, no primary endpoint has been selected, endpoints are not hierarchically ordered or weighted in the analysis and no adjustments for multiplicity will be applied. However, descriptive *p*-values will be provided with appropriate tests.

The full analysis set will be used for the efficacy analyses and the safety set for the safety analyses. Predefined subgroup analyses will be conducted for gender and age groups. Data collected in this trial will be presented using summary tables, patient data listings, and figures. Models such as the analysis of covariance (ANCOVA) and a mixed-effects model for repeated measures (MMRM) will also be explored to compare the efficacy parameters between the treatment groups. For the ANCOVA model, treatment will be included as factor, and baseline value will be included as continuous covariate. The MMRM will incorporate the Huber-White “Sandwich” standard error and will include visit, treatment, visit by treatment as factors, and baseline value (baseline value for the corresponding endpoint analysed) as a continuous covariate. Summary statistics will be provided for demographics, medical/surgical history, and physical examination at baseline and prior/concomitant medication. The homogeneity of treatment groups will be assessed through analysis of baseline characteristics. Additional details of all analyses and data reviews will be provided in the statistical analysis plan (SAP). A draught SAP will be developed prior to the randomisation of the first participant and will be finalised and signed off before the database is locked.

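### Adjustment for baseline confounders is made to depend on observed imbalance, when a short fixed list of prognostic covariates would close the model choice and gain some precision at almost no cost

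*Protocol article*

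**What the plan says.** The Discussion explains why patients with mild-to-moderate depression or anxiety are admitted and names randomised design as the main protection against confounding. It then adds an analysis commitment: "In case treatment groups will be unbalanced in important known potential confounders despite randomization, statistical analysis will account for such differences". It gives no covariate list, no definition of imbalance and no method of adjustment.

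Statistical methods (2.11) plans a baseline comparison: "The homogeneity of treatment groups will be assessed through analysis of baseline characteristics". On the models it says: "For the ANCOVA model, treatment will be included as factor, and baseline value will be included as continuous covariate". The MMRM has visit, treatment and their interaction, plus "baseline value (baseline value for the corresponding endpoint analysed) as a continuous covariate". Baseline PHQ-9 and GAD-7 therefore enter a model only when they are themselves the endpoint.

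The same section calls the analysis exploratory with descriptive p-values. It has the SAP drafted before the first randomisation and signed before database lock. Section 2.4 blinds the data analysts while the trial is in progress.

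**The concern.** The sentence makes observed balance the criterion for adjustment. In a randomised trial that is the wrong criterion. A strongly prognostic covariate is worth adjusting for even when the arms are perfectly balanced, because it removes residual variance. A covariate unrelated to the outcome is not worth adjusting for even when the arms differ on it.

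Two things follow. First, whether the condition is met can be seen only from baseline data split by arm, so the final model is unknown until then. The article contains no list or threshold that would make the step mechanical. With many endpoints at two visits, no primary endpoint and no multiplicity adjustment, a model fixed in advance is one of the few safeguards against selective reporting. Second, in most trials the trigger will not fire for a given covariate, so the precision that covariate offers is lost.

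**Working it through.** **Inputs from the article (Sample size calculation).** Success is defined as "To detect at least one significant outcome in the two cognitive domains memory and executive functioning". The other inputs are d = 0.25, ρ = 0.3 to 0.4 between the two endpoints, two-sided alpha 0.05 per endpoint, a power target of 80%, 15% dropout and 400 randomised. Evaluable: 400 × 0.85 = 340, or 170 per arm at 1:1.

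**Assumptions.** The article gives no figure for prognostic strength, only that in a large cohort "mild to moderate depression had only a limited impact on objective cognitive performance". The partial correlation r between covariate and outcome, after the endpoint's own baseline, is therefore varied: 0.1, 0.2, 0.3 and, as an extreme, 0.5. The imbalance trigger is taken as p < 0.05 on the covariate.

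**1. The plan's own figure.** With SD = 1, the noncentrality is d/√(2/n). Power for at least one success is 1 − P(both |Z| < 1.96) under a bivariate normal with correlation ρ.
- ρ = 0.4: 167 per arm, total 334, and 334/0.85 gives 393.
- ρ = 0.3: 160 per arm, total 320, and 320/0.85 gives 377.
- At 170 per arm, power is 80.8% (ρ = 0.4) to 82.3% (ρ = 0.3).

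The stated 400 is reproduced and the 80% target is met with no extra covariates.

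**2. Gain from fixed adjustment.** Adjustment multiplies the residual variance by 1 − r². Single-endpoint power is approximately Φ(0.25/√(2(1 − r²)/170) − 1.96). Unadjusted: 0.25/0.1085 = 2.305, and Φ(0.345) = 63.5%. The two-endpoint figures hold ρ at its stated value.

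| r | Variance removed (r²) | Single endpoint | At least one of two (ρ 0.4 to 0.3) |
|---|---|---|---|
| none | 0% | 63.5% | 80.8-82.3% |
| 0.1 | 1% | 63.9% | 81.1-82.7% |
| 0.2 | 4% | 65.3% | 82.2-83.7% |
| 0.3 | 9% | 67.6% | 84.0-85.5% |
| 0.5 | 25% | 75.9% | 89.8-91.0% |

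**3. Behaviour of the imbalance-triggered rule.** Simulation with one covariate and 170 per arm, 80,000 null trials and 40,000 trials at d = 0.25 for each r. The reported SE and the true SD of the estimate are under the null.

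| r | Type I error | Mean reported SE / true SD | Power: rule vs always adjusting | Type I error if the better of the two results is reported |
|---|---|---|---|---|
| 0.1 | 4.9% | 0.1084 / 0.1080 | 63.2% vs 63.5% | 5.4% |
| 0.2 | 5.0% | 0.1083 / 0.1082 | 63.3% vs 64.9% | 6.1% |
| 0.3 | 4.7% | 0.1082 / 0.1071 | 63.9% vs 67.4% | 6.4% |
| 0.5 | 4.3% | 0.1077 / 0.1047 | 64.2% vs 75.5% | 7.5% |

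The reported SE is too large by 0.1082/0.1071 − 1 = 1.0% at r = 0.3 and 0.1077/0.1047 − 1 = 2.9% at r = 0.5. Below that there is no clear error. The triggered rule recovers almost none of the available power.

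**4. How often a trigger fires.** For k independent covariates at p < 0.05 the chance of at least one is 1 − 0.95^k: 9.8% (k = 2), 18.5% (k = 4), 26.5% (k = 6), 40.1% (k = 10). With several candidates this is not a rare contingency.

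**The case against.** The strongest reply is that little is at stake and much is unsettled. The sentence is Discussion prose, and accounting for differences could mean a supplementary analysis. The covariate list and trigger are normal SAP content, and the SAP is not shown. If the SAP fixes both before lock, the rule becomes mechanical. The analysis is exploratory and the analysts are blinded. Most of this stands and limits the weight of the point. It does not remove it, because the article states the principle that balance decides adjustment, and a SAP that follows it faithfully inherits the weakness.

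A reader might infer three stronger things, none of which the article supports:

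- **That the rule produces false positives.** Applied mechanically it errs the other way, with type I error at or below 5%. Inflation appears only if the better of two results is chosen, which the article does not propose.
- **That the sentence contradicts section 2.11.** There the ANCOVA and MMRM are described as models to be explored, with details left to the SAP, and the baseline comparison is not tied to covariate selection. There is a loose fit, not a firm conflict.
- **That the trial is underpowered for lack of covariates.** The figure of about 63.5% is single-endpoint power. The plan is powered for at least one of two domains, and that target is met.

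Larger gains, such as those from covariates jointly explaining 10-20% of residual variance, rest on figures the article does not give. For depression alone its own text suggests a weak effect, so r of 0.1-0.2 is the plausible range. It does say that fatigue and other factors weigh more on cognition, and it calls age a risk factor, so somewhat larger values are possible once those are included.

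**Conclusion.** The point holds as a poor stated method with modest consequences. Conditioning adjustment on observed imbalance uses the wrong criterion, leaves the model open until baseline data are seen by arm, and gives up precision. For r of 0.1-0.3, the loss against fixed adjustment is about 0.4 to 4 percentage points of single-endpoint power (63.9 − 63.5 to 67.6 − 63.5) and about 0.3 to 3 points of the plan's two-endpoint power. The type I error of the mechanical rule is about 4-5%. The sample size and its 80% target are unaffected. These sizes rest on the assumed r and the assumed p < 0.05 trigger; the direction does not depend on the exact values. The change is worth making because it is nearly free, not because the trial's validity is threatened.

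**What to change.** Replace the conditional sentence with a short fixed list of prognostic baseline covariates, used in every efficacy ANCOVA and MMRM whatever the observed balance, alongside the endpoint's own baseline. Age, PHQ-9, GAD-7 and MFIS are natural candidates: Table 3 shows demographics and all three scales at the baseline visit. Where one of these is itself the endpoint, its baseline enters once. Education or time since infection should be added only if they are recorded as data items, since Table 3 does not itemise them. Settle the list in the SAP before any baseline data are viewed by arm. Report baseline comparability descriptively and do not use it to choose covariates. If the sponsor wishes to keep an imbalance-driven adjustment, label it a sensitivity analysis.

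The cost is SAP wording and a few degrees of freedom out of about 340 evaluable patients. The core list needs no new data.

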## Glossary

CVLT: California verbal learning test
d2-R: d2 test of attention-revised
eCRF: electronic case report form
GAD-7: generalised anxiety disorder 7-item
GCP: good clinical practise
ICH: international council for harmonisation
IEC: independent ethics committee
IRT: interactive response technology
MedDRA: medical dictionary for regulatory activities
MFIS: modified fatigue impact scale
mPEM-DSQ: modified post-exertional malaise subscale questions from DePaul symptom questionnaire
PCFSS: post COVID functional status scale
PCS: post COVID-19 syndrome
PCR: polymerase chain reaction
PEM: post-exertional malaise
PHQ-9: patient health questionnaire-9
SAP: statistical analysis plan
SARS-CoV-2: severe acute respiratory syndrome coronavirus 2
SBQ-LC: symptom burden questionnaire for long COVID
TMT (A + B): trail-making test parts A and B
